### Study population and design

2.1

The THECORW study is a prospective cohort study. A total of 825 radiation workers will be recruited in Chongqing from 2024 to 2044. The study aims to include radiation workers in Chongqing. In accordance with the regulations on occupational health management of radiation workers issued by the National Health Commission of China, occupational health management is mandated for all radiation workers nationwide (34). Consequently, all radiation work units in Chongqing are required to organize regular occupational health examinations for radiation workers, with the interval between two consecutive examinations not exceeding 2 years (34). Radiation workers registered in the Chongqing CDC personal dose monitoring system will receive information about the study during their annual occupational health examinations from our investigators. Workers who consent to participate will provide written informed consent before enrollment. Those meeting the inclusion criteria will be enrolled in the study. Following enrollment, their personal dose monitoring data from the Chongqing CDC personal dose monitoring system will be integrated with health data from National Radiation Health Information Platform via personal identification numbers (35). Participants will retain the right to withdraw from the study at any time and for any reason without any consequences.

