### Statistical analysis

2.5

Health examination outcomes and individual dose monitoring data will be collected from Chongqing CDC personal dose monitoring system and National Radiation Health Information Platform (35, 40). Data quality will be assessed using the “dataquieR” package in R software, following the framework proposed by Schmidt et al. (52, 53). If radiation dose data is missing, we can use the notional dose to supplement the missing data, which represented the average dose for the same occupation during that year (54). The exposure–lag–response association between radiation dose and health outcomes will be evaluated using a distributed lag non-linear model (DLNM) combined with either a generalized linear model (GLM) or multiple generalized additive models (GAM) (55). For certain outcomes, if necessary, a nested case–control design will be applied, with controls time-matched to cases to ensure a comparable number of total person-time observations. A cross-basis function in the DLNM, utilizing natural spline basis functions, will be employed to construct a two-dimensional matrix that integrates radiation dose and lag time, thereby enabling a detailed analysis of the lag structure (55). For continuous health outcomes, a Gaussian distribution will be used as the link function; for count outcomes, a Poisson distribution will be applied; and for categorical outcomes, a binomial distribution will be employed in the GLM framework. Given the non-linear relationship between radiation dose and health outcomes, GAM will be applied to assess potential dose–response relationships. For non-linear relationships, piecewise linear spline models will classify participants into different exposure categories based on radiation exposure thresholds and will use these categories to assess linear dose–response relationships. Several sensitivity analyses were conducted to assess the robustness of the results. First, GAM or GLM analyses will be rerun after excluding cases with missing data for both controls and cases. Second, to account for potential interaction effects, interaction models were fitted by including variables such as exposure dose levels, age, gender, and occupational category in relation to health outcomes. Third, if significant interaction effects were identified, stratified analyses were performed, such as by occupational category or exposure dose levels, to explore these effects further. All analyses were carried out using R software (version 4.4.1). For normally distributed data, continuous variables are presented as mean ± standard deviation (SD); skewed data are presented as median or interquartile range (IQR). *p* values <0.05 were considered as statistically significant.

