## Health outcomes

3

Radiation workers undergo routine health examinations at the Chongqing CDC, health examination outcomes will be collected from the National Radiation Health Information Platform (35). These evaluations encompass a comprehensive set of assessments, including complete blood count, biochemical blood analysis, urinalysis, audiometry, thyroid function tests, ophthalmic examinations, dermatological assessments, micronucleus analysis, and chromosome aberration analysis, among them, the complete blood count is the primary health outcome. All examinations were conducted by the Health Examinations Department. The outcomes of these health evaluations are monitored to identify potential radiation-related health risks.

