## Discussion

4

This article outlines the study protocol for investigating occupational exposure among radiation workers in Chongqing, providing valuable insights and methodological strategies for cohort studies in the region. Despite the increasing awareness of chronic low-dose ionizing radiation exposure, the exposure-lag response associations with various adverse health outcomes remain underexplored, highlighting the need for further research in this area.

Some progress in the cross-sectional survey has been made in the occupational investigation of radiation workers with different health outcomes in China. Regarding the effects of occupational radiation exposure on the complete blood count, Zhang et al. (3) noted that low-dose ionizing radiation could increase the detection rate of abnormal white blood cells in radiation workers, yet no significant effect on hemoglobin and platelets. However, the influencing factors such as years of service and type of work were not further analyzed, which were closely related to the abnormal health outcome (4). Wang et al. showed that the occupational population had a higher risk of white blood cell and platelet counts, while no significant effect was observed on red blood cell counts (4). The cross-sectional survey design made it impossible to monitor the progression of health outcomes over an extended period. In contrast, a cohort study design incorporating longitudinal data enables the evaluation of temporal effects on health outcomes, facilitating the investigation of both long-term cumulative exposure-response relationships and exposure-lag-response dynamics.

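### Section 2.5 names GLM or GAM for blood counts repeated on the same workers and provides nothing for within-worker correlation, so standard errors for persistent dose differences would be too small

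*Protocol article*

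**What the plan says.** All references are to the protocol article.

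- **Model (section 2.5, Statistical analysis).** The exposure–lag–response association is to be estimated with a "distributed lag non-linear model (DLNM) combined with either a generalized linear model (GLM) or multiple generalized additive models (GAM"). The abstract repeats the GAM/GLM choice.
- **Families (section 2.5).** "For continuous health outcomes, a Gaussian distribution will be used as the link function; for count outcomes, a Poisson distribution will be applied". Categorical outcomes get a binomial distribution. Significance is judged at p<0.05.
- **Outcome (section 3).** "the complete blood count is the primary health outcome".
- **Examination schedule (section 2.1).** Regular examinations are mandatory, "with the interval between two consecutive examinations not exceeding 2 years". Workers are told of the study "during their annual occupational health examinations from our investigators".
- **Calendar span (section 2.1).** "A total of 825 radiation workers will be recruited in Chongqing from 2024 to 2044".
- **Purpose (section 4, Discussion).** The case for the design over cross-sectional surveys is that "a cohort study design incorporating longitudinal data enables the evaluation of temporal effects on health outcomes".
- **Alternative design (section 2.5).** "For certain outcomes, if necessary, a nested case–control design will be applied".

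The listed sensitivity analyses deal with missing data, interactions and stratification. Nowhere does the article mention a worker-level term, a correlation structure, a variance estimator that allows for clustering, or one record per worker.

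**The concern.** The design produces several blood counts per worker, and counts from one person resemble each other over time. The models named for them, as commonly fitted, treat each row as a fresh independent observation.

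The harm depends on how dose varies. Cumulative dose carries earlier exposure forward. Section 2.6 also shows that average dose differs by occupation (0.74 mSv a year in industrial work against 0.56 mSv overall). Part of the dose contrast is therefore likely to be a lasting difference between workers. For that part, ten counts on one worker carry much less information than ten counts on ten workers, and an independence model overstates the precision.

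The result would be confidence intervals that are too narrow, and too many false-positive dose or lag associations for the primary outcome. For contrasts made purely within a worker the error reverses: the naive standard error is too large and real effects may be missed.

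**Working it through.** **Inputs from the article.** Examinations are annual or at most two years apart. The span 2024 to 2044 is at most 20 years, so one worker has at most about 20/2 = 10 examinations on a two-yearly schedule, or about 20 on a yearly one. The significance level is 0.05. The number of workers after loss is 660 (660/(1−0.20) = 825, as stated). The article gives no figure of its own for within-worker correlation, so there is none to reproduce.

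**Assumed inputs.** Outcome ICC 0.3 to 0.7; dose ICC 0.25 to 1.

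**Formulas.** For a slope fitted as if rows were independent, with m examinations per worker:

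- variance inflation D = 1 + (m−1) × ICC_outcome × ICC_dose
- true SE / naive SE = √D
- true type I error = 2 × (1 − Φ(1.96/√D))

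**Results**

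| m | outcome ICC | dose ICC | D | SE ratio | type I error |
|---|---|---|---|---|---|
| 10 | 0.3 | 0.25 | 1 + 9×0.075 = 1.675 | 1.29 | 0.13 |
| 10 | 0.5 | 0.5 | 1 + 9×0.25 = 3.25 | 1.80 | 0.28 |
| 10 | 0.7 | 1 | 1 + 9×0.7 = 7.3 | 2.70 | 0.47 |
| 20 | 0.3 | 0.25 | 1 + 19×0.075 = 2.425 | 1.56 | 0.21 |
| 20 | 0.5 | 0.5 | 1 + 19×0.25 = 5.75 | 2.40 | 0.41 |
| 20 | 0.7 | 1 | 1 + 19×0.7 = 14.3 | 3.78 | 0.60 |
| any | any | 0 | 1 | 1.00 | 0.05 |

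**Fewer visits for late entrants.** Suppose entry is spread evenly, so that m runs from 1 to 10. The size-weighted mean is (1²+…+10²)/(1+…+10) = 385/55 = 7.

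- ICCs 0.3 and 0.25: D = 1 + 6×0.075 = 1.45, SE ratio 1.20, type I error 0.104.
- ICCs 0.5 and 0.5: D = 1 + 6×0.25 = 2.5, SE ratio 1.58, type I error 0.215.

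**Within-worker contrasts.** If dose is centred within each worker, its ICC is −1/(m−1), and D becomes 1 − ICC_outcome. At outcome ICC 0.5 the true SE is √0.5 = 0.71 of the naive one, so the naive test is conservative.

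**Simulation check.** With 660 workers, no true effect, outcome ICC 0.3 to 0.7, dose ICC 0.25 to 0.9 and 1,000 runs per setting, the naive test rejected in 12% to 46% of runs at m=10 and 22% to 60% at m=20. Worker-clustered standard errors brought this to 4% to 7%.

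**Closer to a lag model.** A further simulation assumed skewed doses (lognormal, mean 0.56 mSv, log-SD 0.8 between and 0.6 within workers), 10 two-yearly visits and 400 runs. At outcome ICC 0.3, 0.5 and 0.7, the naive test of cumulative dose rejected in 27%, 39% and 43% of runs. A naive joint test of six lags rejected in 15%, 18% and 24%.

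**The case against.** **The article does not say that examinations are independent rows.** It names a model family and outcome distributions but never defines the analysis record. A GAM can carry a worker random effect, and a GLM can be reported with clustered variance. Both would fit section 2.5 as written. This stands: a reader might infer that the plan commits to treating every examination as independent, but that is an inference from the named models.

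**It could be left to an analysis plan that is not shown.** This stands only in part. Section 2.5 goes down to spline type, outcome families, sensitivity analyses and software version. The model class it fixes at that level, used as named, does not suit repeated measurements, which are the stated reason for the design.

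**Follow-up per worker is unknown.** A reader might infer that every worker contributes 10 or more counts over 20 years. The article does not support this: 2024 to 2044 is worded as a recruitment period, 20% loss is allowed for, and no follow-up length per worker is given. Late entrants will have fewer counts.

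**The largest figures are extremes.** A reader might also take 1+9×ICC_outcome, with standard errors understated 1.9 to 2.7 fold, as the expected size. That needs dose to be constant within each worker, whereas the study is about time-varying dose. In the simulation above, the joint lag test, which is nearer to the planned analysis, was less inflated than the cumulative-dose test.

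**The nested case–control option** with one record per worker would avoid the problem. It is optional, applies to certain outcomes only, and does not clearly cover a continuous blood count.

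**Conclusion.** The point holds as a mismatch between the named model class and the data. Outcomes are repeated on the same workers, the models are GLM or GAM, and nothing is provided for within-worker correlation. If the models are fitted as named with one row per examination, the inference on dose and lag for the primary outcome is not valid.

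The direction is firm under stated conditions. With positive within-worker correlation in both outcome and dose, type I error exceeds 5% for any m above 1. With no within-worker correlation in dose there is no inflation, and for purely within-worker contrasts the naive error is too large.

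The size is not known, because every ICC and the number of visits per worker are assumptions. For up to 10 visits, the cases worked above put type I error at about 10% to 47%: 13% to 47% if all workers have 10, and 10.4% and 21.5% for the two ICC pairs at an effective m of 7. Annual examinations over the full 20 years would give more, but that is a ceiling and not an expectation.

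**What to change.** Keep the DLNM cross-basis and the outcome families. State in section 2.5 that it is fitted in a GAMM/GLMM with a worker random effect, or that GEE or cluster-robust variance by worker ID is used. State that all intervals and tests of the dose–lag surface rest on that fit. Say what one analysis record is. If a case–control set with one record per worker is used for some outcome, name that outcome.

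The cost is a sentence or two and standard R code, with no new data: records are already linked by personal identification number (section 2.1). The statistical price is wider intervals for cumulative-dose effects.

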### Sample size calculation

2.3

Radiation exposure damages hematopoietic tissues, which is characteristic of occupational exposure. It has been proven that the hematological system, including mature functional cells, is susceptible to ionizing radiation (36). Ionizing radiation can cause early damage to the hematological system, therefore, blood cell counts are commonly used to assess its effects, a method widely used in the field (36).

The complete blood count served as the basis for sample size calculation. A sample size of 825 is considered sufficient to allow studies of the impact of radiation on human health. For example, according to references, the white blood cell count is commonly used to assess the effects of radiation on the health of a population (3, 4). The average white blood cell count for the population in the Chinese radiation group is (6.34 ± 1.40)*10 (9)/L, and in the normal population group is (6.59 ± 1.39)*10^9^/L.^5^ For a type I error of 0.05, a type II error of 0.1, and a power of 0.9, the sample size required is 660. Considering a 20% loss in follow-up (37, 38), the sample size increases to 825. Therefore, a recruitment sample of 825 radiation-exposed individuals will have sufficient power for the study. The sample size was estimated using G*Power software version 3.1 (Heinrich-Heine-Universität Düsseldorf, Düsseldorf, Germany) (39).

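### The optional time-matched nested case-control design saves no data collection in a fully linked cohort, would cost precision if used, and has no matching-aware analysis named for it

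*Protocol article*

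**What the plan says.** All references are to the protocol article.

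- **Design option (section 2.5, Statistical analysis):** for some outcomes and only if needed, "a nested case–control design will be applied, with controls time-matched to cases to ensure a comparable number of total person-time observations". The closing words give the reason for sampling. No outcome, control ratio or further matching variable is named.
- **Model (section 2.5):** outcome types are mapped to distributions, and "for categorical outcomes, a binomial distribution will be employed in the GLM framework".
- **Sensitivity analysis (section 2.5):** "GAM or GLM analyses will be rerun after excluding cases with missing data for both controls and cases". This suggests that the GLM or GAM is also the model for sampled cases and controls.
- **Data (section 2.1):** after enrolment each worker's dose record "will be integrated with health data from National Radiation Health Information Platform via personal identification numbers". Section 2.6 takes covariates from the dose monitoring system, and section 3 takes examination results from the national platform.
- **Cohort size (section 2.1):** "A total of 825 radiation workers will be recruited in Chongqing from 2024 to 2044".
- **Dose over time (section 2.6, repeated in section 4):** the average annual dose in Chongqing fell overall from 2016 to 2020. The text does not give the size of the fall.

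**The concern.** Nested case-control sampling pays when exposure or covariates are costly to obtain, because only cases and a few controls then need to be measured. That reason is absent here, since every enrolled worker's dose history and results are to be linked. The stated reason, comparable person-time, does not replace it. A model built on risk sets or on person-intervals already accounts for workers being observed for different lengths of time.

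Two things are at stake if the option is taken up. The first is precision, mainly for sparse binary secondary outcomes. In the 50 workers of Table 1, lens opacity was abnormal in 2 and hearing loss was present in none. A cross-basis over dose and lag needs several parameters, and such outcomes can least afford to lose information.

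The second is validity. Selecting controls at the cases' times gives cases and controls the same distribution of time. If the analysis then leaves time out while dose depends on time, the dose odds ratio is attenuated. Timing of exposure is the study's central question, so the handling of time matters.

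**Working it through.** **The plan's own figure.** The article gives no figure for the case-control option. The cohort size used below can be reproduced. With means 6.34 and 6.59 (difference 0.25), pooled SD √[(1.40² + 1.39²)/2] = 1.395, two-sided 5% and 90% power, n = 2 × (1.960 + 1.282)² × 1.395² / 0.25² ≈ 655 per group, against the stated 660. Then 660/0.8 = 825. Nothing below rests on this calculation except N = 825.

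**Is there anything to save?** Dose (section 2.1), covariates (section 2.6) and outcomes (section 3) are routine electronic data. Section 2.4 derives organ and lens doses from dosimeter readings by formula and describes no extra collection for a subset. Computing is no obstacle either: 825 workers over at most 20 years give at most 825 × 20 = 16,500 worker-years.

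**Precision.** Near the null, with k controls per case, relative efficiency against the full cohort is k/(k+1), and the standard error grows by √[(k+1)/k].

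| k | Efficiency | SE factor |
|---|---|---|
| 1 | 0.50 | 1.41 |
| 2 | 0.67 | 1.22 |
| 4 | 0.80 | 1.12 |

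**Share of workers unused.** If a proportion p become cases, at most (1 + k)p of the workers are used. The values of p are assumptions.

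| p | Unused at 1:1, at least | Unused at 1:4, at least |
|---|---|---|
| 2% | 96% | 90% |
| 4% | 92% | 80% |
| 10% | 80% | 50% |
| 20% | 60% | 0% |

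**Simulation.** All settings are assumptions: 825 workers, 20 yearly visits, about 70 cases, true odds ratio 1.5 per SD of exposure between workers within a year, one linear exposure term without lags, and 100 runs per scenario. Mean exposure stayed flat, or fell over the 20 years by about 1 SD (moderate) or 3 SD (strong). Controls were drawn at the case's visit, 1:1 or 1:4.

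- *SD of the log odds ratio:* full cohort 0.11–0.13; conditional logistic 0.17–0.20 at 1:1 and 0.14–0.15 at 1:4. The scenario ratios to the full cohort are 1.39–1.59 and 1.17–1.30. They are in line with the formula or somewhat worse, as can happen away from the null and with 100 runs.

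| Analysis of the sampled sets | Mean odds ratio (true 1.5) |
|---|---|
| Conditional logistic | 1.48–1.55 |
| Binomial GLM adjusting for time | 1.48–1.55 |
| Binomial GLM without time, no dose trend | 1.51–1.54 |
| Binomial GLM without time, moderate fall | 1.43–1.45 |
| Binomial GLM without time, strong fall | 1.25–1.27 |
| Unconditional GLM, one indicator per set, 1:1 | 2.1–2.4 |
| Unconditional GLM, one indicator per set, 1:4 | 1.6–1.7 |

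The last two rows rest on at most 25 runs each. The 1:1 row agrees with the known doubling of the log odds ratio in that model (1.5² = 2.25).

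**The case against.** The strongest reply is that this is a conditional option in a condensed article. Which outcomes would use it, with what control ratio and what likelihood, may stand in a full protocol or analysis plan that is not shown. The binomial sentence is a general mapping from outcome type to distribution and is not tied to the case-control sentence. Nothing says that time would be left out of the model. With matching on time alone, a conditional likelihood is not required, because a binomial model that adjusts for time does as well. The primary outcome, the complete blood count, is hardly touched. All of this stands, and the silence on outcomes, ratio and likelihood is not held against the article.

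It also rules out three stronger readings.

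- *That most of the cohort is discarded.* The option may never be used, and the unused share ranges from nil to 96% over the values tried. Unused workers are not lost information in equal measure either: at 4% cases and 1:4 sampling at least 80% of workers are unused, yet about 20% of the information is lost near the null.
- *That lens opacity will give about 33 cases (4% of 825), so that 1:1 sampling keeps 66 workers.* The 2/50 in Table 1 is a 2016 prevalence, whereas this design uses new cases, and workers with cataract are excluded at entry. Even as a prevalence its exact 95% interval is 0.5% to 13.7%, or about 4 to 113 of 825.
- *That the odds ratios will be biased toward 1.* This needs both omission of time and a dose trend during follow-up. The reported trend covers 2016–2020, before recruitment starts in 2024. One indicator per set would err in the opposite direction.

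What the objection does not answer is the rationale. The article gives a reason for sampling, and in a linked cohort that reason does not support it.

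**Conclusion.** The point holds in a limited form. As written, the nested case-control option has no data-saving purpose, and its stated purpose is better met by a full-cohort model. If it is used, precision falls at any finite control ratio: the standard error rises by about 41% at 1:1 and 12% at 1:4 near the null. The burden would fall mainly on sparse binary secondary outcomes.

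Bias is a possibility and not a finding about the plan. Under the assumed settings, a binomial GLM without the matching time moved an odds ratio of 1.5 to between 1.25 and 1.45, depending on the size of the dose trend. It caused no attenuation without a trend, and adjustment for time removed it. The documents do not give the trend's size over 2024–2044, the control ratio or the number of cases, so no single figure can be put on the loss or on the bias in this study.

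**What to change.** In section 2.5, replace the nested case-control sentence with a full-cohort analysis of binary and incident outcomes. Use the same dose–lag cross-basis in a discrete-time model (pooled logistic or complementary log-log) or in a Cox model with delayed entry. The discrete-time form suits outcomes seen only at periodic examinations, and delayed entry suits workers who join at different times. Either handles unequal person-time directly.

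If the option is kept for any outcome, name that outcome and the reason for sampling. Analyse the sets by conditional logistic regression, or by a binomial model that explicitly adjusts for the matching time. Do not enter one indicator per matched set in an unconditional model.

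The change is a sentence or two of text. It needs no extra data and slightly more computing.

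### Section 2.5 applies Poisson to count outcomes without saying which outcomes these are or allowing for dispersion; the primary blood cell counts should be placed explicitly under the Gaussian rule

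*Protocol article*

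**What the plan says.** Section 2.5 (Statistical analysis) picks the model family by type of outcome. The continuous rule reads "For continuous health outcomes, a Gaussian distribution will be used as the link function" (Gaussian is a family rather than a link, but the intent is clear). The count rule reads "for count outcomes, a Poisson distribution will be applied". Categorical outcomes get a binomial model. The section does not list which outcomes fall under which rule. It does not mention a dispersion parameter, a negative binomial model or a robust variance.

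Section 3 (Health outcomes) states that "the complete blood count is the primary health outcome". Section 2.3 (Sample size calculation) says that "blood cell counts are commonly used to assess its effects" and works with the white blood cell count; the Discussion speaks of red cell and platelet counts. No other outcome is called a count. Chromosome aberrations and micronuclei (sections 3.2.3 and 3.2.4) are described as rates with normal ranges.

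Table 1 (section 2.6), however, reports white cells, red cells and platelets as concentrations with mean ± SD, the format that section 2.5 gives for normally distributed continuous variables. Section 2.3 likewise compares two white cell means using their SDs.

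**The concern.** A Poisson model takes its standard errors from the assumption that the variance equals the mean. If that is false, the test of dose at a given lag has the wrong size or loses power even when the mean model is right. For a concentration there is a further problem: the ratio of variance to mean depends on the unit, so the p-value does too.

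Read literally, the word count sends the main components of the primary outcome to Poisson. Read with Table 1, the same components are Gaussian. The two readings can give opposite inferences from the same data. The sensitivity analyses in section 2.5 (excluding missing data, interactions, stratification) do not vary the family, so they would not be expected to expose the problem. The issue is also separate from repeated examinations, since it arises with a single examination per worker.

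**Working it through.** **1. The plan's own figure.** For two means with difference 6.59 − 6.34 = 0.25, SD 1.40, two-sided 5% and 90% power:

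n = 2 × (1.960 + 1.282)² × 1.40² / 0.25² ≈ 659, rounded up to 660 per group; 660 / 0.80 = 825.

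This matches the stated 660 and 825. It shows that section 2.3 handles white cells as a continuous variable. (That 660 is a per-group figure is a separate matter.)

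**2. Variance-to-mean ratio φ = SD² / mean, from Table 1 (50 workers, 2016).**

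| Measure | Mean ± SD | φ |
|---|---|---|
| White cells (10⁹/L) | 5.72 ± 1.46 | 2.13 / 5.72 = 0.37 |
| Red cells (10¹²/L) | 4.88 ± 0.65 | 0.42 / 4.88 = 0.087 |
| Platelets (10⁹/L) | 214.32 ± 58.01 | 3365 / 214.32 = 15.7 |

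Poisson requires φ = 1. The Poisson standard error would be about 1.6 times too large for white cells (1/√0.373), 3.4 times too large for red cells (1/√0.087), and 4.0 times too small for platelets (√15.7).

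**3. Consequence if these were modelled as Poisson.** A nominal 5% Wald test rejects under no effect with probability 2 × [1 − Φ(1.96/√φ)]. For an effect that a correct test finds with 90% power (z = 1.960 + 1.282 = 3.24), Poisson power is close to 1 − Φ(1.96/√φ − 3.24).

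- Platelets: 1.96/3.96 = 0.495, so the false-positive rate is 62%.
- White cells: 1.96/0.610 = 3.21. The false-positive rate is 0.1%, and power is 1 − Φ(−0.03) = 51%. With the section 2.3 figures for radiation workers (6.34 ± 1.40, φ = 0.31) power is 39%.
- Red cells: 1.96/0.294 = 6.66, so power is 1 − Φ(3.42), below 0.1%.
- Unit: white cells per microlitre are 1000 times the tabulated value, so φ becomes 373 and the false-positive rate 92%, against 0.1% in the tabulated unit.

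**4. Simulation.** With 660 workers, one observation each and an assumed lognormal dose, 2000 runs under no effect gave plain Poisson rejection rates of 62% (platelets), 0.1% (white cells), 0% (red cells) and 92% (white cells × 1000). Quasi-Poisson and Gaussian fits to the same data gave 4.7% to 5.6%, whatever the unit. In 1000 runs at the 90%-power effect, Poisson found 49% for white cells and 0% for red cells, against 89% and 91% with quasi-Poisson or Gaussian.

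**5. If the blood counts are Gaussian.** The Poisson rule is then left for true tallies, such as micronuclei or aberrations if analysed as numbers per cells scored. The documents give no dispersion for these, so φ is an assumption. The formula in step 3 gives false-positive rates of 8% at φ = 1.25, 11% at 1.5, 17% at 2 and 26% at 3.

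**The case against.** The strongest reply is that nothing assigns the blood counts to Poisson. Concentration units, mean ± SD and a two-means sample size all point to Gaussian. The complete blood count also includes hemoglobin and hematocrit, which are not counts on any reading, and white blood cell count is simply the laboratory's name for the test. This stands. A reader might infer that the plan commits its primary outcome to Poisson, and that 62% is therefore the study's false-positive rate for platelets; the documents do not support that.

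Second, this is a condensed article, and a full analysis plan could deal with dispersion. This stands in part: silence does not forbid a dispersion adjustment. But the article does name a distribution, and it names it for a class of outcomes that it does not define.

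Third, Table 1 gives marginal variances from 50 workers, not residual variances from the planned model. This is true but does not rescue Poisson. Normal-theory 95% intervals for φ, holding the mean fixed, are about 11 to 24 for platelets, 0.26 to 0.58 for white cells and 0.06 to 0.13 for red cells; none includes 1. Covariates would have to explain 1 − 1/15.7 = 94% of the platelet variance to bring φ to 1. For white and red cells, adjustment moves φ further below 1.

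Fourth, the cytogenetic results are described as rates with cut-offs and could fall under the binomial rule instead. This stands, so the figures in step 5 illustrate a range and are not evidence about this cohort.

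**Conclusion.** The point holds as an ambiguity with a harmful literal reading. Section 2.5 does not say which outcomes are counts and allows for no dispersion, and the only outcomes the text calls counts are part of the primary outcome.

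If they were analysed as Poisson, the document's own figures imply roughly 62% false positives for platelets, 51% instead of 90% power for white cells, near-zero power for red cells, and unit-dependent p-values. These sizes are conditional on that reading, on one examination per worker and on the marginal variances in Table 1. The more natural reading is Gaussian, under which none of them applies.

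What then remains is the use of Poisson without a dispersion allowance for any true tallies. It is anti-conservative if they are overdispersed, by an amount the documents do not allow one to fix. It would go too far to say that the documents show such overdispersion. The change is worth making because it is cheap and closes off the damaging reading of the primary analysis.

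**What to change.** Make two changes in section 2.5.

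1. State that white cell, red cell and platelet concentrations are continuous outcomes and are analysed under the Gaussian rule.
2. Replace the Poisson sentence with one saying that true tallies (for example micronuclei or chromosome aberrations, if analysed as numbers per cells scored) will be analysed with a quasi-Poisson or negative binomial model, log link, and the log of the number of cells scored as offset.

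The cost is a sentence or two of text and a different family in the R model call; the cross-basis for dose and lag is unchanged. Intervals become slightly wider where tallies are overdispersed, which is the correction intended. Where they are not, almost nothing is lost.
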